### How to inform men’s decision making for *BRCA1/2* germline mutations genetic testing

The other aim is to investigate how to inform men’s decision-making. Low levels of men’s knowledge regarding *BRCA1/2* germline mutations is found as one of the most important problems in this field [40]. Therefore, one main research achievement may be to find a right way to correctly inform them. The present study aims to test two different messages tailored on men’s specific needs and to understand what is the best strategy to inform them. Although narrative approaches showed efficacy in promoting health behavioral intentions [41], and in increasing adherence to cancer screening [42] in particular, its utility for improving men’s *BRCA* cascade screening remains unexplored. The present research intends to explore whether narrative messages can be effective in informing men’s decision-making.

In particular, two features are fundamental in narrative strategies context: the narrative perspective and the framing. The first one is a fundamental story feature and changes how information is delivered to the audience; researchers identified that first-person narrative messages are able to increase self-identity and to promote the assimilation of the theme better than third-person narratives [43]. Therefore, the present study chooses to create narrative messages with a first-person feature. Regarding the framing, messages can either emphasize negative consequences (losses) or positive outcomes (gains) of a given action. Prospect theory [44] posits that, in general, people are more likely to take risks when presented with a loss-framed message, and the contrary for a gain-framed message. But regarding disease prevention behaviors, like smoking cessation [45] and skin cancer prevention [46], researchers have suggested an advantage, albeit small, of a gain frame over a loss frame [47]. Therefore, the present study chooses to create narrative messages oriented to a gain frame.

Furthermore, applying the Uncertainty Management Theory [48], a social psychological approach to uncertainty, Rauscher et al. [14] investigated how men with increased *BRCA*-related cancer risk approach the individual and familial uncertainty related to that pathogenic variant. Those qualitative results showed that men’s primary concern when managing *BRCA*-related cancer risks is the aversive consequences of the discovery of a germline mutation for their family [49]. Their focus on familial uncertainty management is maybe due to the difficulties encountered in the management of their own risk due to the lack of information and management options. In the end, the authors suggested that genetic counseling would benefit a family focus. Also, Hallowell and colleagues [50] highlighted the role of family members (mother, partner, or children) in men’s decision-making about BRCA testing. In particular, they showed how men’s decision to have genetic testing was influenced by the obligations perceived from family members, primarily their children.

Based on these premises, this study protocol proposes to test the effectiveness of two first-person gain-framed messages, one narrating a self-referred story and the other a family-referred story. The effectiveness will be measured in terms of one or both messages ability to predict the intention to undergo the genetic screening.

### Hypotheses

We hypothesize the following relationships (Fig 1 shows the tested model):

HP1: higher risk perception, positive outcome expectations and action self-efficacy longitudinally predict the intention to undergo genetic test for BRCA germline mutations.HP2: higher health risk attitude and low intolerance to uncertainty have a longitudinal influence on predicted higher intention, planning and action initiation.HP3: higher intention and coping self-efficacy longitudinally predict higher planning.HP4: higher planning (i.e., action planning, coping planning) and coping self-efficacy longitudinally predict higher action initiation.Based on results by Rauscher et al. [14] and Hallowell and colleagues [50], we formulated a research question: (RQ1) is there any difference between personal outcome expectations and family outcome expectations in their association with intention?HP5: family-referred narrative gain framed message (vs. self-referred narrative gain framed message) will produce greater intention and action to undergo genetic testing for *BRCA 1/2* germline mutations in at-risk men.

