#### Time 1 assessment

All participants will complete the T1 assessment, via an online survey which will be available for a two-week period. The T1 measures will include demographic, health status, risk perception, health risk aversion, and intolerance of uncertainty. After this evaluation, participants will be randomized and exposed to one message. A manipulation check, the evaluation of the perceived quality of the information presented on the messages, positive outcome expectations, action self-efficacy, benefit for genetic test will be then collected. The constructs of trust in doctors and health literacy included in the original study protocol approved by the Ethical Committee have been not integrated here.

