#### Time 2 assessment

The original study protocol approved by the Ethical Committee included a T2 assessment with questions on intention to undergo germline genetic testing and evaluation of the quality of the message content, and a subsequent (3–4 weeks later) T3 with coping self-efficacy, action planning, and coping planning. Since the HAPA model does not state that there should be a waiting time between the measurement of the intention and the coping/action planning, we collapse T2 and T3. Therefore, one-two weeks after the administration of T1, via an online survey, participants reply to questions on intention to undergo germline genetic testing, coping self-efficacy, action planning, and coping planning.

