### T2 measures

After the message exposure, participants reply to several questions.

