**Hypothesis 1.** Predictors will be: risk perception, positive outcome expectations, action self-efficacy. Covariates: demographic, health status. Outcome variable will be: intention to undergo genetic test for BRCA germline mutations.**Hypothesis 2.** Predictors will be: health risk attitude, intolerance to the ambiguity. Covariates: demographic, health status. Outcome variables will be: intention to undergo genetic test for BRCA germline mutations, action and coping planning, action initiation.**Hypothesis 3.** Predictors will be: intention to undergo genetic test for BRCA germline mutations, coping self-efficacy. Covariates: demographic, health status. Outcome variables: action and coping planning.**Hypothesis 4.** Predictors will be: action and coping planning. Covariates: demographic, health status. Outcome variable: action initiation.**Research question 1.** Predictor variable: positive outcome expectations (personal vs family). Outcome: intention to undergo genetic test for BRCA germline mutations.**Hypothesis 5.** Predictor variable: treatment/message (family-referred narrative gain framed message vs. self-referred narrative gain framed message). Outcome variables: intention and action to undergo genetic testing for *BRCA 1/2* germline mutations.

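### HP3 claims longitudinal prediction of planning, but its predictors and outcomes are all measured once, in the same T2 survey

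*Protocol article*

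**What the plan says.** The Hypotheses section of the protocol article states HP3 as "higher intention and coping self-efficacy longitudinally predict higher planning". The Statistical analyses section carries the same variables into the model: "Predictors will be: intention to undergo genetic test for BRCA germline mutations, coping self-efficacy", and then "Outcome variables: action and coping planning".

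The Time 2 assessment section explains that the ethics-approved protocol measured intention at T2 and had "a subsequent (3–4 weeks later) T3 with coping self-efficacy, action planning, and coping planning". It then says "we collapse T2 and T3", on the ground that HAPA requires no waiting time between intention and planning. Under the schedule now in force, one to two weeks after T1 "participants reply to questions on intention to undergo germline genetic testing, coping self-efficacy, action planning, and coping planning". The Time 3 assessment section confines the new T3 to action initiation, recorded over the 3 months after T2.

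On the items answered after the message, two sections differ. Time 1 assessment puts message exposure inside T1 and, after naming the manipulation check and the message-quality ratings, says "positive outcome expectations, action self-efficacy, benefit for genetic test will be then collected". The Measures section has a T1 block for what is answered before randomization. A block headed T2 measures follows, which opens "After the message exposure, participants reply to several questions" and holds those same five measures alongside intention, coping self-efficacy and planning.

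**The concern.** A longitudinal claim needs the predictor to be measured before the outcome. For HP3 it is not. With one reading per construct, taken from one self-report survey, timing does not rule out the reverse direction: a man who has already worked out when and where to be tested may for that reason report a firmer intention. Answering habits or mood on the day can also raise all the scores together. Neither can be told apart from prediction, so a report that intention or coping self-efficacy predicted planning over time would go beyond the data.

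The article also plans direct, indirect and total effects, and its account of HAPA treats intention as a mediator between the motivation and volition phases. If a path through intention to planning is among those estimated, its last leg is cross-sectional.

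The second matter is one of consistency. HP1 is also stated as longitudinal, and the manipulation check decides who is excluded. Both depend on whether the post-message items belong to T1 or to T2.

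**Working it through.** No stated figure is at issue, so the check sets each predictor's wave beside its outcome's wave, using the Time 1, Time 2 and Time 3 assessment sections, the Measures section and the hypothesis list under Statistical analyses.

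| Link | Predictor measured | Outcome measured | Lag, current text |
|---|---|---|---|
| HP3: intention → planning | T2 | T2 | 0 |
| HP3: coping self-efficacy → planning | T2 | T2 | 0 |
| HP1: risk perception → intention | T1, before message | T2 | 1–2 weeks |
| HP1: outcome expectations, action self-efficacy → intention | T1 after message (Time 1 section), or T2 (Measures heading) | T2 | 1–2 weeks, or 0 |
| HP2: health risk attitude, intolerance of uncertainty → intention, planning | T1 | T2 | 1–2 weeks |
| HP2: same predictors → action | T1 | T3 | at least 1–2 weeks |
| HP4: planning, coping self-efficacy → action | T2 | T3 | up to 3 months |

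**HP3.** Both rows are zero. The article describes no earlier measure of intention or coping self-efficacy and no later measure of planning, so no other pair of readings could supply a lag.

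**What the merger changed.** In the ethics-approved schedule intention was at T2 and planning at T3, 3–4 weeks later, so that lag fell from 3–4 weeks to zero. Coping self-efficacy was already in the old T3 with action and coping planning, so its lag was zero then and is zero now.

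**HP1.** Risk perception is at T1, before the message, in both sections. The other two predictors are at T1 by the Time 1 section and under T2 by the Measures heading. The Time 2 section's list of T2 content contains none of the post-message items, so it agrees with the Time 1 section. Two schedule sections therefore stand against one heading. The sentence under that heading says only that the items follow the message, which is true of either wave.

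**Illustration of what a shared occasion can do.** The documents give no figure for this, so the shares below are assumptions. Take two scores with no relation except a common same-occasion component making up a share *s* of each score's variance, so that their expected correlation is *s*. With n = 132 (the total from the article's power calculation), a two-sided 5% test of the correlation, and 4,000 simulated samples per setting:

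| *s* | Proportion significant |
|---|---|
| 0 | 0.04 |
| 0.1 | 0.22 |
| 0.2 | 0.64 |
| 0.3 | 0.94 |

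This shows that a significant same-survey association need not reflect prediction. It does not estimate how much shared variance this trial will have.

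**The case against.** The best defence is that the merger is disclosed and reasoned. HAPA, as the article reads it, asks for no interval between intention and planning, so measuring them together is legitimate. That stands: the merger is not itself an error. It justifies the joint measurement, however, and does not make the resulting association longitudinal.

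It can also be said that the old 3–4 week gap would not have excluded reverse direction or shared self-report variance, since neither schedule describes a baseline measure of planning. This is fair and limits what the merger cost, but the current text still claims a time order that it does not have.

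Several stronger readings are tempting, and the documents do not support them:

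- A reader might infer that the merger removed a lag for all of HP3. It did so only for intention to planning.
- A reader might infer that the Measures section makes HP1 wholly a same-session analysis. Risk perception is at T1 in both places, so at most two of its three predictors are affected.
- A reader might infer that the manipulation check is really a recall test given 1–2 weeks later. That rests on one heading, probably mislabelled, against two schedule sections.
- A reader might infer that the article commits itself to an indirect effect through intention to planning. The Statistical analyses section names no indirect path, and Fig 1, which would show the tested relations, is not available here.

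Reach is limited too. The primary hypothesis is the message comparison (HP5), which does not depend on HP3's time order, and the secondary objective names intention and action rather than planning.

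**Conclusion.** The point holds for HP3 as worded. Intention, coping self-efficacy, action planning and coping planning are measured once, in one T2 survey; the lag is zero for both predictors, and only a concurrent association can be estimated. The loss due to the merger is the 3–4 week lag for intention to planning, and nothing for coping self-efficacy.

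This rests on the schedule in the Time 2 and Time 3 assessment sections being the one run, and on the T2 survey being a single occasion. If some men complete it over several days, the article still fixes no order between predictors and outcomes.

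The labelling conflict is real but secondary, and most likely a heading error. If the Time 1 section is followed, HP1 keeps its 1–2 week lag and the manipulation check comes straight after the message. Only if the Measures heading were followed would two HP1 predictors lose their lag and the check become a delayed one.

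**What to change.** 1. In the Hypotheses section, reword HP3 as a concurrent association at T2 between intention and coping self-efficacy on one side and planning on the other.
2. In the Statistical analyses section, state that any indirect effect containing the intention-to-planning path will be reported as cross-sectional on that path.
3. Reserve 'longitudinal' for links from T1 to T2, T1 to T3 and T2 to T3, that is HP1, HP2 and HP4.
4. In the Measures section, move the manipulation check, message quality, positive outcome expectations, action self-efficacy and perceived benefit into a block labelled 'T1, after message', matching the Time 1 and Time 2 assessment sections. The authors should first confirm that this is the schedule in use.

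The cost is a few sentences of text, with no change to data collection or sample size. The downside is a weaker claim for HP3.

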**Fig 1 pone.0266327.g001:**
[figure not shown]
Expected relations between variables. T1, T2, T3 indicate the three different timeframes of the research.

## Method

### Design plan

The research will involve three phases, with results from each phase informing the next phase (see Fig 2). In the first phase, a literature review will be performed to identify other psychological variables influencing individuals’ adherence to evidence-based guidelines on *BRCA1/2* germline genetic testing. Subsequently, a pilot survey will be created in order to test its feasibility and understandability for participants. The third and final phase entails an experimental study analyzing the proposed hypotheses.

**Fig 2 pone.0266327.g002:**
[figure not shown]
The three phases of the research project.

### Study plan

The experiment conducted in the third phase will be a Randomized Control Trial with participants receiving one of the two conditions (i.e., self-referred narrative framed message, family-referred narrative framed message) and it tests the main hypotheses and research question of the study. Participants will answer several questions before and after the message/treatment exposure.

### Blinding

Participants will not know the treatment group to which they have been assigned. Personnel who interact directly with the study subjects will not be aware of the assigned treatments (i.e., double-blinded). Personnel who analyze the data collected from the study will be aware of the treatment applied to the given groups; however, they will not interact directly with the participants to ensure double-blindness.

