#### Manipulation check

Two items created ad hoc evaluate whether participants have read and understood the message content. Multiple-choice answers are used with one correct answer and two incorrect answers as distractors. Participants who fail to answer those questions will be excluded from the analyses.

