### Ethical considerations

Ethical approval has been acquired from the local ethics committee of the IEO (approval number R1249/20-IEO 1314). Participation is voluntary. All data will be collected in a pseudo-anonymized form. Data will be analyzed in an anonymous form. Data will be treated confidentially and used only by the collaborators in the present study for scientific purposes. No adverse effects are expected for participants; in case of necessity, personal contact of the main researchers will be shared with them.

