### Statistical analyses

Data exclusion: The answers to the manipulation check will be analyzed before the main analyses to see whether participants have read the message until the end, understood, and recalled the content.

Missing data: presence of missing data will be checked before conducting the main analyses. If a subject does not complete T1 and T2 that subject will be excluded from the analysis.

Normality of the data will be checked before conducting the main analyses. Non-normality will be handled applying either non-parametric tests or SEM with estimator for non-normal distribution.

Statistical analyses will be performed in SPSS version 25 and the *Lavaan* and *SemPaths* packages in RStudio software.

Preliminary analysis: Pearson’s r correlations among variables.

Main analyses: the hypotheses 1, 2, 3, and 4 will be tested either using structural equation modeling (SEM) or multiple regressions. Research question 1 will be tested either using structural equation modeling (SEM) or ANOVA. In case of non-normality in the data, WLSMV will be applied and the Satorra-Bentler scaled test statistic and robust standard errors were used. In the model specification, the factor loading of the first indicator of each latent variable will be set to 1. The following goodness-of-fit indices will be used to evaluate model-data correspondence: the Chi-square value, the Comparative Fit Index (CFI), and the Root Mean Square Error of Approximation (RMSEA). The model will be considered as acceptable when the CFI is higher than .90 and close to .95 and when the RMSEA is .08 or less. Finally, modification indices and the matrix of standardized correlation residuals will be inspected for potential improvement of model fit. Direct, indirect (or mediate), and total effects were also estimated. To test hypothesis number 5 an ANCOVA will be applied.

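### Analysts will know the arms while choices that shape the primary message comparison (HP5) are still open; the arms should be coded and those choices locked first

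*Protocol article*

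**What the plan says.** Under Blinding, the article says of the analysts: "Personnel who analyze the data collected from the study will be aware of the treatment applied to the given groups". It adds one safeguard: "they will not interact directly with the participants to ensure double-blindness". The same section makes clear that its double-blind label covers participants and the staff who deal with them.

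HP5 is the primary hypothesis (Hypotheses; Primary and secondary outcomes). It predicts that the family-referred message will do better than the self-referred one on intention and action. Statistical analyses assigns it to an ANCOVA. Four other statements decide which men and which model enter that test:

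- **Manipulation check.** There are two multiple-choice items, each with one correct answer, and then: "Participants who fail to answer those questions will be excluded from the analyses".
- **Order of work.** Statistical analyses says: "The answers to the manipulation check will be analyzed before the main analyses". It gives missing data and normality the same place in the sequence.
- **Completeness and non-normality.** A man who does not complete T1 and T2 is dropped. On distribution: "Non-normality will be handled applying either non-parametric tests or SEM with estimator for non-normal distribution".
- **Covariates.** Sample size and power calculation counts seven. The list by hypothesis names covariate groups for HP1 to HP4 and none for HP5.

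**The concern.** Keeping analysts away from participants stops them influencing the answers men give. In this trial the answers come through an online survey, so that route is already narrow. Bias can also enter later, when someone decides who is excluded and which model is fitted, and lack of contact does nothing there.

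The people handling the data will know which group read the family message, and the hypothesis says that group should score higher. Where the text allows two readings, the choice between them can be made, knowingly or not, with the direction of the result in view. This would affect the credibility of the primary comparison.

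**Working it through.** The plan gives no figure on this point, so there is none to reproduce. The check has two parts.

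**1. What remains open for HP5**

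| Decision | What the article fixes | What it leaves open |
|---|---|---|
| Manipulation-check exclusion | Two items, one correct answer each; reviewed before the main analyses | Whether failing one item or both excludes |
| Completeness | Men not completing T1 and T2 are dropped | Whether missing either assessment or only missing both excludes |
| Method | ANCOVA for HP5 | Whether the non-normality clause displaces it; the clause gives two routes and no criterion |
| Covariates | Seven counted in the power calculation | Which ones; none is listed for HP5 |

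Two features make these more than formal gaps. The messages differ after a common introduction (Intervention), so failure on the check could differ by arm. Intention is measured with three 5-point items, so the non-normality clause may well be triggered.

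**2. What directional choice can do**

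Input: alpha of .05 (Sample size and power calculation). For a two-group comparison this is 2.5% in each direction.

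Let z1 and z2 be the test statistics of two admissible analyses, positive when the family message does better. There is no true difference, and the analyst reports the larger.

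- False positive for the family message, independent analyses: 1 − 0.975² = 1 − 0.950625 = 0.0494, or 4.94%.
- False positive for the self message: 0.025² = 0.000625, or 0.06%.
- Sum: 4.94% + 0.06% = 5.0%.

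The two-sided total does not move. The error shifts almost wholly into the predicted direction. With perfectly correlated analyses the family-direction rate stays at 2.5%, and with positive correlation it lies between 2.5% and 4.94%.

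Real alternatives use largely the same men and the same outcome, so they are correlated. A null simulation (4,000 runs each at N = 132 and N = 264) shows how much this matters. Taking the smaller p over one two-way choice gave between 6.85% and 7.725%. The choices tried were ANCOVA or Mann-Whitney, one or both check items, and with or without covariates. By symmetry about half falls in each direction: 6.85% / 2 = 3.4% and 7.725% / 2 = 3.9%. The simulation assumes 8% failure per check item and three prognostic covariates out of seven; neither figure is in the article.

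The 4.94% limit is for one two-way choice. Several choices combined are not bound by it.

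**The case against.** The strongest reply has four parts.

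- **The label is honest.** The article says whom double-blind covers and discloses that analysts know the arms. This stands: a reader might infer that the plan contradicts itself, but it does not.
- **The checks come first.** Exclusions, missing data and normality are all reviewed before the main analyses. This limits the risk, because followed strictly it means these decisions precede the HP5 test. It fixes an order but not a mask, and it does not cover the covariate set.
- **Scoring is objective and the test is named.** Each check item has one right answer, the action outcome is an event, and HP5 has an ANCOVA. All true. The latitude lies in the exclusion rule, the completeness rule, the non-normality clause and the covariates.
- **Some detail belongs in an analysis plan that is not shown.** Fair, and so the point is not raised as missing detail. That analysts know the arms is a design choice the article states outright.

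Three stronger readings are tempting, and the documents do not support them.

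- A reader might count the choices between SEM and regression, between SEM and ANOVA, and the model changes from modification indices. These serve HP1 to HP4 and RQ1, which as listed do not have the message as predictor. Knowing the arms gives no handle there and coding them would not help; a rule set in advance would.
- A reader might quote 1 − 0.95² = 9.75% as the error rate. That is the rate for taking the smaller p in either direction from two independent tests. An analyst with A/B-coded data could do the same, so it does not measure what masking prevents.
- A reader might infer from the offer of the main researchers' contact (Ethical considerations) that analysts will meet participants. Nothing says those researchers analyse the data, and Blinding expressly rules out such contact.

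**Conclusion.** The point holds in a limited form. The analysts know the arms by design, the stated safeguard does not reach analysis decisions, and four decisions bearing on HP5 remain open in the article.

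For one two-way choice made in favour of the family message, the false-positive rate in that direction rises from 2.5% to at most 4.94%. That limit assumes independent analyses and an analyst who always takes the more favourable one. Under the simulation's assumptions, correlated analyses give roughly 3.4% to 3.9%. These figures show what the text permits; they do not predict what the analysts will do. An analysis plan not shown may already close some of the choices. The change is worth making because it lowers a real risk to the primary comparison at almost no cost. It does not show the design to be invalid.

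**What to change.** 1. Give the analysts a data set with the arms coded A/B.
2. Before the code is broken, and before outcomes are compared between A and B, record in a dated note: whether one or both failed check items exclude; how incomplete T1 and T2 data are treated; the normality decision; and one method and one covariate set for HP5.
3. If the check items reveal the arm, have a team member outside the outcome analysis score them and pass on only whether each man passed.
4. Reword Blinding to describe this, and to say what the no-contact rule does and does not protect.

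Steps 1 and 2 are both needed. Coding stops a choice from favouring the family message, and the lock stops selection of the smaller p-value, which coding alone would allow.

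The cost is a recoded column, a short note and a wording change. No participants or study visits are added, and sample size and power do not change. The article says no data had been collected when the plan was submitted for preregistration; if collection has since begun, the steps can still be taken before the code is broken.
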